## 2.8 Economic evaluation

The economic analysis will take a NHS perspective covering the intervention costs, NHS and personal social service (PSS). The impact on cost effectiveness of out-of-pocket spending and employment will be assessed. Data will be collected by patient monthly report, supplemented by a brief case notes review for non-responders, and a detailed notes review on 5–10% of participants to check precision of self-reported data. Quality of Life (QOL) will be measured by EQ-5D-5L at baseline, 3 months 6 months and 12 months. QALYs will be estimated by means of area under the curve. The differences for Cost and QALYs between interventions will be estimated adjusted for baseline characteristics. Where appropriate we will estimate incremental cost-effectiveness ratios (ICERs) for comparing different interventions. Bootstrapping will generate incremental cost effectiveness ratios (ICERs). Cost-effectiveness acceptability curves will be produced to reflect the probability of an intervention being cost-effective at different willingness-to-pay values per QALY gained. Major assumptions made in the analysis will be tested by means of sensitivity analyses.

## 2.9 Process evaluation

We will conduct a mixed-methods process evaluation to examine uptake and engagement with the trial interventions and trial procedures and explore potential mechanisms of action and contextual factors that may influence intervention delivery and outcomes.

**Qualitative:** A purposive sample of up to 100 patient participants (final numbers to be determined considering information power [38]) will be invited to take part in a semi-structured telephone interview at least 3 months after randomisation each year/phase of the trial. The sample will include participants from each of the four intervention arms; and a range of ages, genders, ethnicities, deprivation level, education, risk factors for infections, history of RTIs, self-reported beliefs about RTIs, self-reported behaviour (physical activity, stress management, nasal spray use), and intervention usage. An interview topic guide was developed to explore participants’ experiences of the intervention and the trial processes and procedures, identify barriers and enablers to intervention engagement, perceived benefits of the intervention, impact of the COVID-19 pandemic on their preventative behaviours and intervention use. Interviews will be transcribed verbatim and transcripts will be managed using NVivo qualitative data management software and analysed using reflexive thematic analysis [39]. We will examine how and why our qualitative findings converge with, complement, or contradict the quantitative findings.

**Quantitative:** Analysis of the process questionnaire data and usage data will assess intervention reach (uptake; sample characteristics), self-reported adherence to the nasal sprays and getting active and healthy paths interventions, predictors of adherence and outcomes (age; gender; education; comorbidities; RTI and behavioural beliefs; barriers to behaviour change. We will examine the moderator effects of baseline characteristics (particularly demographics) on intervention engagement and outcomes, and the factors likely to mediate engagement (e.g. behaviour, beliefs). We will also employ multi-level modelling to investigate how process measures relate to outcomes and intervention engagement.

## 2.10 Patient and public involvement

Two public contributors with experience and understanding of respiratory issues contributed to the overall design of the study and are full collaborators on the programme grant.

Three public contributors assisted during the development of the digital interventions used in this trial. This included taking part in think-aloud interviews, working through sections of the interventions with a researcher. This helped to refine the interview topic guides and ensure the language and communication was more broadly appropriate. Two contributors also reviewed and commented on early drafts of the intervention pages and automated emails, and reviewed the nasal spray instruction videos and written materials.

During development of the trial processes and materials, the public contributors piloted the baseline and outcome questionnaires to ensure feasibility and clarity, and have reviewed all participant-facing documentation.

Three public contributors are full members of the Trial Stakeholder group. They will attend monthly stakeholder meetings and contribute to management decisions regarding development and operationalising the trial. They will also contribute to the writing up of trial outputs including publications and lay summaries.

## 2.11 Monitoring

### 2.11.1 Data monitoring and oversight

An independent trial steering committee (TSC) will be convened to provide trial oversight. The TSC will also provide the function of the Data Monitoring and Ethics Committee (DMEC) as the interventions and the trial processes are considered low risk.

Monthly management meetings with key stakeholders including co-investigators, collaborators, trial management and public contributors will be held throughout the trial period.

### 2.11.2 Adverse event reporting

Any adverse events reported by participants or by the GP surgery will be documented and reviewed for severity, expectedness and relatedness to the trial and trial interventions. Serious adverse events (SAEs) will be reviewed for expectedness. The trial includes elderly and high-risk patients so a high rate of planned or emergency hospitalisations, new illness diagnoses, worsening of pre-existing conditions, cardiovascular events, falls, and deaths are expected in this population. These events will be documented and reviewed by the chief investigator. All SAEs including serious adverse device effects (SADEs) that are unexpected or considered *possibly*, *probably* or *definitely* related to the trial or interventions, will be reported to the sponsor and the REC immediately and followed up with a detailed written report.

### 2.11.3 Discontinuation and withdrawal of participants

If a participant expresses a wish to withdraw from the trial treatment (e.g. does not wish to use the nasal sprays or advice from the Getting Active/Healthy Paths website), the trial team will explain the importance of follow-up and ask if they would be willing to continue in the trial without using the interventions and complete the questionnaires. This will be recorded in the participants records. If the participant does not confirm continuation or requests full withdrawal, the participant will be withdrawn from the trial and receive no further communication from the trial team. All data collected up to the point of withdrawal will be used, unless the participant has specifically requested for it to be deleted.

If a participant moves to a new GP practice, the trial team will endeavour to contact the new practice and ask if they would notify the team of any SAEs during the trial period.

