#### 2.3.2 Comparator: Usual care with brief advice about managing infections

Participants allocated to usual care will receive a brief page of advice about managing respiratory tract infections, based upon NHS current advice (rest, keeping warm, fluids, over-the-counter medications for symptom relief). Specific resource use will be tracked for health economic analysis. The usual care group will be asked not to use any over-the-counter nasal sprays during the trial period. After 12 months, participants will be offered access to the digital intervention promoting physical activity and stress management for a short time.

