### 2.7.2 Data analysis

A detailed statistical analysis plan will be developed prior to data analysis. IBM® SPSS® software platform, Stata and Excel software will be used to evaluate outcomes.

The primary analysis will be based on those who report at least one infection in a normal year (before COVID). We will also conduct a sensitivity analysis to include all participants who included under the broader inclusion criteria (‘at-risk’ due to COVID).

The primary time point for analysis will be at 6 months. The analysis of the primary outcome and other continuous outcomes will compare all groups. For the incidence of infection data the primary analysis will be between each intervention group and usual care, and if any of these demonstrate an intervention is effective then we propose secondary comparisons between groups. A secondary analysis will use repeated measures over the year.

The particular regression models used will depend on the data and the patterns of residuals but we anticipate logistic regression models for dichotomous outcomes, negative binomial models for count data, and generalised linear mixed models will be used for continuous variables (all controlling for baseline values; stratification variables and potential confounding variables). Intention to Treat (ITT) analysis with missing data imputed (via chained-equations multiple imputation model) will be the primary analysis, and complete cases as a sensitivity analysis. Secondary analyses will follow a similar modelling approach to the primary analyses. The repeated measures analysis over the one-year period will allow for the clustering of observations within participants over time. Estimates will be provided for key subgroups (e.g. those with recurrent infections (>3/year), age >65, the presence and number of serious comorbidities). Results will be reported in line with the CONSORT guidelines.

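### A participant who asks to stop the intervention and does not then confirm staying in follow-up is not contacted again, which can add avoidable missing outcomes, probably mainly in the three active arms

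*Protocol article*

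**What the plan says.** Section 2.11.3 (Discontinuation and withdrawal of participants) starts from a stated wish: "If a participant expresses a wish to withdraw from the trial treatment". The examples it gives are a participant who "does not wish to use the nasal sprays or advice from the Getting Active/Healthy Paths website". The team then explains why follow-up matters and will "ask if they would be willing to continue in the trial without using the interventions and complete the questionnaires". The next sentence sets the default: "If the participant does not confirm continuation or requests full withdrawal, the participant will be withdrawn from the trial and receive no further communication". Earlier data are protected: "All data collected up to the point of withdrawal will be used, unless the participant has specifically requested for it to be deleted".

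Three other places bear on this:

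- Section 2.7.1 (Data collection) provides monthly emails with a one-week reminder. Non-completers at 6 months also get a paper questionnaire after 2 weeks and a telephone call after 3–4 weeks, because 6 months is the primary time point.
- Section 2.7.2 (Data analysis) makes the primary analysis "Intention to Treat (ITT) analysis with missing data imputed" by chained equations.
- Section 2.3.2 describes the comparator: "Participants allocated to usual care will receive a brief page of advice about managing respiratory tract infections". It adds one restriction: "The usual care group will be asked not to use any over-the-counter nasal sprays during the trial period".

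**The concern.** The default gives a missing answer the same consequence as an explicit request to leave. A participant may decline only the spray or the website, say nothing against questionnaires, and still lose all later outcome collection. An intention-to-treat analysis needs outcomes whether or not people keep using the intervention, so the rule works against the analysis it feeds.

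If such losses occur mainly in the arms that have something to stop, and if people stop because of side effects, illness or no perceived benefit, missingness depends on both arm and outcome. Multiple imputation that assumes data are missing at random may not correct this, least of all for someone withdrawn early who leaves few monthly reports to impute from.

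**Working it through.** **1. Who is still followed up.** Reading sections 2.11.3 and 2.7.1 together:

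| Participant | Later outcome collection |
|---|---|
| Stops using the intervention and tells no one | Monthly emails and reminders; paper and telephone at 6 months |
| Does not return the 6-month questionnaire | Paper and telephone |
| Tells the team they wish to stop, agrees to stay | As for any participant |
| Tells the team they wish to stop, does not confirm | None |
| Asks to leave the trial | None |

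The fourth row is the problem. This person has not declined follow-up, yet is pursued less than an ordinary non-responder.

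**2. Which arms.** The named treatments are the nasal sprays (two arms) and the Getting Active/Healthy Paths website (one arm). Usual care has an advice page. That the default acts mainly in the active arms is an inference from these two sections.

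**3. The plan's follow-up assumption (section 2.6).** 147/0.15 = 980 per group; 980 × 4/0.80 = 4900; 4900 × 3 strata = 14,700. All three figures reproduce. One 80% follow-up figure serves all arms, so the plan allows for no imbalance.

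**4. Effect on power.** The document gives no withdrawal rate, so assume that each active arm loses an extra share *w* of 1%, 2%, 5% or 10%. No SD is given either. For a 1-day difference with two-sided alpha 0.01 (sidedness is my assumption) and 90% power, 147 per group implies SD = √[147/(2 × (2.576 + 1.282)²)] ≈ 2.22 days. This value is used only to scale the loss.

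- Active *n* = 147 × (0.80 − *w*)/0.80, against 147 in usual care.
- Power = Φ(1/[2.22 × √(1/147 + 1/*n*)] − 2.576).
- Retained of 4900 (1225 per arm) = 1225 × 0.80 + 3 × 1225 × (0.80 − *w*).

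**5. Effect on bias.** Let *d* be the mean illness days of those lost minus that of those retained. If *m* is the retained mean, the full mean is (1 − *w*)*m* + *w*(*m* + *d*) = *m* + *wd*. If imputation treats the lost like the retained, the active-arm mean is too low by *wd*.

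| *w* | Active follow-up | Retained of 4900 | Active *n* | Power | Bias, *d* = 1 | Bias, *d* = 4 |
|---|---|---|---|---|---|---|
| 0 | 80% | 3920 | 147.0 | 90.0% | 0 | 0 |
| 1% | 79% | 3883 | 145.2 | 89.8% | 0.01 | 0.04 |
| 2% | 78% | 3847 | 143.3 | 89.6% | 0.02 | 0.08 |
| 5% | 75% | 3736 | 137.8 | 88.9% | 0.05 | 0.20 |
| 10% | 70% | 3553 | 128.6 | 87.5% | 0.10 | 0.40 |

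**6. Why these biases are upper values.** They treat the whole 6-month outcome as lost and assume that the changed default recovers everyone. If half of those affected would not respond anyway, and half of their excess days fell in months already reported (both assumptions), the bias that the fix could remove is 0.5 × 0.5 = one quarter of the table: 0.0025 to 0.10 days.

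**7. Yardstick.** The 1-day target applies to infected participants. Using the infection rates in section 2.6, it averages 0.40 × 1 = 0.40 days over everyone in stratum 2, about 0.60 in stratum 3 and 0.65 to 0.71 in stratum 1. Only the extreme corner of the table (*w* = 10%, *d* = 4) reaches the smallest of these.

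**The case against.** The strongest reply is that the rule is narrow and humane. It applies only after a person has contacted the team, been told why follow-up matters, been asked to stay, and not agreed. Failing to confirm can also mean declining or answering ambiguously, and ending contact then protects people from being chased. Intention to treat with multiple imputation can accommodate some withdrawals, and a complete-case sensitivity analysis is planned. The number of attempts and the waiting time may be set out in the full protocol, which is not shown.

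Much of this stands, and it limits what may be claimed. A reader might infer four stronger things that the document does not support:

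- *That anyone who stops using the intervention is withdrawn.* The trigger is an expressed wish; silent non-users stay in follow-up.
- *That outcome data are discarded.* Data up to withdrawal are used unless deletion is requested. What is lost is later collection, and those gaps are imputed.
- *That the rule is confined to the active arms.* The treatments are listed as examples, and full withdrawal is open to all. Usual care is asked to avoid sprays and may have outcome-related dropout of its own, so the net direction of bias is not established.
- *That the loss comes on top of the planned 20%.* The 80% figure may already include such withdrawals, and stratum 3 follow-up is reported as just under 80%. The total loss might then be no larger, though still uneven between arms.

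The reply does not justify the default itself. An explicit refusal can be honoured without treating an unanswered question as one.

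**Conclusion.** The point holds in a limited form. Section 2.11.3 fixes a default that ends outcome collection for some people who have not declined it, including the contact that section 2.7.1 provides to secure the primary outcome. This can add avoidable missing data, probably mainly in the three active arms and plausibly related to participants' experience of the intervention.

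The size is unknown. Under the assumed 1–10% extra active-arm loss, the cost in power is small, at about 0.2–2.5 percentage points. Bias is the larger risk: at most about 0.01–0.40 days if those lost have 1–4 more illness days, and less if earlier months were reported or some would not respond in any case. If those lost are sicker, the error favours the active arms; if they are less ill, it reverses. This is a cheap improvement worth making. It does not show that the trial is materially biased.

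**What to change.** Reverse the default in section 2.11.3. A participant who stops the intervention and does not reply to the request to continue stays in questionnaire follow-up, including the 6-month paper and telephone contact, unless they explicitly decline follow-up. Put an easy opt-out in every contact. Record stopping the intervention and withdrawing from follow-up as separate events, with dates, and report both by arm. For participants already withdrawn under the present wording, report the same split where records allow; section 2.11.3 already requires something about the request to continue to be recorded.

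The cost is a short amendment to the withdrawal wording and to the website and email scripts, plus a few more reminders to people who had not replied. Explicit requests to leave are honoured as now, and nothing about treatment changes.

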## 2.12 Ethics and dissemination

### 2.12.1 Research ethics approval

This trial was approved by the South East Scotland Research Ethics Committee 01 (20/SS/0102) on 23^rd^ October 2020 and the HRA on 29^th^ October 2020.

### 2.12.2 Consent

All participants will receive information and will have the opportunity to ask questions prior to deciding whether to take part. For the main trial, participants will give consent online after registering on the Immune Defence website. For participants taking part in a telephone interview, written consent or verbal consent over the telephone will be given by the participant to the researcher.

### 2.12.3 Dissemination

The results of the trial will be disseminated in peer-reviewed journals and presented at primary care conferences. All participants (GP practices and patient participants) will be sent an accessible copy of the findings by email within 6 months of trial completion (unless they have opted out of further contact). We will also disseminate our findings to the wider public via our patient collaborators, PPI panels and through social media.

Findings will report anonymised data and summary statistics. No information identifying individual participants or GP practices will be reported. Trial records will be retained for a minimum of 10 years after the trial has been published.

## 3 Discussion

RTIs generate symptoms which are the major driver of winter consultation pressures. Most are viral in aetiology, so limiting viral replication and load through use of nasal sprays, could reduce symptom burden and healthcare consultations, providing an evidence-based alternative to antibiotics. Similarly, if an intervention to promote physical activity and stress management can be shown to reduce the number and severity of infections this will provide significant motivator for those who suffer with recurrent infections to use the intervention. Providing patients with alternative strategies to antibiotics is likely to modify patient beliefs and expectation, reduce antibiotic use, and alter subsequent help seeking behaviour [6, 7, 32, 33]. This is also likely to be relevant during pandemic winters. SARS-CoV-2 is transmitted in similar ways to other respiratory viruses, thus nasal sprays that reduce viral load have the potential to reduce COVID-19 as well as usual winter illnesses. The brief physical activity and stress management intervention is likely to be as pertinent during the pandemic winters, particularly as levels of anxiety and stress will be higher, and maintaining a good level of physical activity has been strongly encouraged.

The trial has been designed to assess the impact in groups of individuals who are at high risk for infections/adverse outcomes. These include individuals who report frequent recurrent infections but with no significant comorbidities; individuals with serious comorbidities/risk factors alone; and those with both recurrent infections and comorbidities/risk factors. Thus, it is plausible that either an intervention to use a web-based applications to modify stress and increase physical activity, or alternatively advice to use an inexpensive and easily available nasal spray, could both help symptom control, de-medicalise infections, and be widely implemented among the broad group of patients suffering recurrent infections.

### 3.1 Status and timeline

This trial is funded as part of the NIHR PGfAR RECUR Programme. The development and optimisation of the trial platform was nearing completion in March 2020 and we had planned a large feasibility trial in the 2020–21 winter season followed by a full trial in the following 2021–2023 seasons. However, with our experiences of conducting similar large trials together with support from the funder, we felt able do a very much larger full trial starting in the 2020–2021 winter season. This allows us to provide information not only about whether such interventions are likely to work in a pandemic season but also in more ‘normal’ winters for respiratory illnesses.

Recruitment of participants commenced in December 2020 and is expected to be completed by April 2023. The last participant will complete the trial by end April 2024. The current version of the protocol is v8.1 dated 15-11-2022.

There have been two main amendments to the trial in response to the changing landscape of the COVID pandemic. In season 1 we included participants aged 65+ considered higher risk of COVID-19. From Season 2 onwards we tightened the inclusion criteria to include 65+ who also reported at least 1 RTI in a normal year (before COVID). We considered this would give a better chance of participants engaging with our interventions. In season 3 we are focussing recruitment on participants with comorbidity/risk factors, and not recruiting any further participants aged 65+ without any other risk factors for infection.
